#### Stepwise addition of metformin

The stepwise addition of metformin is done at 6, 12, 18, 24, or 30 months for intervention arm participants who, despite 6 months of lifestyle interventions, are considered to be at the highest risk of conversion to diabetes, defined as having IFG + HbA1c ≥ 6.0% or IFG + IGT. Metformin is prescribed at a starting dose of 250 mg twice daily followed by up-titration to 500 mg twice daily after 3 months if the participants do not experience any side effects. If participants experience side-effects with metformin, the dose is adjusted by the study investigators accordingly. Once added, metformin is prescribed for the remaining study period, ranging from 6 (i.e., added at month 30) to 30 months (i.e., added at month 6). Metformin is discontinued at the end of the study or at the point of diabetes conversion.

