### Endpoints

#### Primary endpoint

The primary endpoint is the proportion of participants who develop diabetes within 3 years from the baseline visit. Diabetes is diagnosed on the basis of a single FPG of ≥ 7.0 mmol/L or a 2-h plasma glucose of ≥11.1 mmol/L, in accordance with the criteria of the American Diabetes Association [31]. An FPG test is conducted every 6 months, and an OGTT is conducted annually.

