### Statistical analyses

The primary effectiveness analysis will be carried out on the modified intention-to-treat (ITT) population, consisting of all randomized participants who are present for at least one follow-up visit. The risk of prediabetes-to-diabetes conversion at 3 years will be modeled using a generalized linear model (GLM) with an identity link function and binomial variance function. Potential confounders such as age, sex, family history of diabetes and FPG at baseline will be included as covariates. The risk difference between the intervention and control groups and its 95% confidence interval will be reported. The risk of diabetes conversion at months 6, 12, 18, 24, and 30 will also be analyzed using the modified ITT set.

Sensitivity analyses will be performed on the ITT population. Multiple imputation datasets will be generated using chained equations [40], and the imputed datasets will be analyzed using the same GLM and covariates as the primary effectiveness analysis. In addition, two supportive analyses will be conducted: (i) the Kaplan-Meier estimator will be used to compare the cumulative incidence of diabetes in intervention and control participants, and (ii) the proportional hazards model for interval-censored data will be used to analyze the time to diabetes onset. The hazard ratio between the two study arms and its 95% confidence interval will be reported. The same analyses will be performed using the per-protocol population (all randomized participants who (i) have provided FPG and OGTT results at the study conclusion, and (ii) if they are in the intervention arm, have attended the goal-setting workshop, at least one nutrition workshop and at least one exercise session).

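### The per-protocol rule requiring month-36 FPG and OGTT makes membership depend on attendance after the outcome is known, so a participant diagnosed earlier is dropped, event included, if the final OGTT is missing

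*Protocol article*

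**What the plan says.** All references are to the protocol article.

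- **Endpoint (Primary endpoint).** "The primary endpoint is the proportion of participants who develop diabetes within 3 years from the baseline visit". One value is enough: "Diabetes is diagnosed on the basis of a single FPG of ≥ 7.0 mmol/L or a 2-h plasma glucose of ≥11.1 mmol/L". On timing: "An FPG test is conducted every 6 months, and an OGTT is conducted annually". Table 3 accordingly schedules FPG at months 6, 12, 18, 24, 30 and 36, and the OGTT at months 12, 24 and 36.
- **Per-protocol set (Statistical analyses).** There are two numbered criteria. Criterion (i), for both arms, is that participants "have provided FPG and OGTT results at the study conclusion". Criterion (ii) is that, "if they are in the intervention arm, have attended the goal-setting workshop, at least one nutrition workshop and at least one exercise session". Neither makes an exception for a participant already diagnosed.
- **Use of the set (Statistical analyses).** "The same analyses will be performed using the per-protocol population". The sentence follows the binomial model for the 3-year risk, the Kaplan-Meier comparison and the proportional hazards model for interval-censored data.
- **Other sets (Statistical analyses).** The primary analysis uses a modified ITT set, "consisting of all randomized participants who are present for at least one follow-up visit". Sensitivity analyses use multiple imputation on the ITT population.
- **After conversion (Stepwise addition of metformin).** "Metformin is discontinued at the end of the study or at the point of diabetes conversion". The article does not say whether converters continue study visits or repeat the OGTT.

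**The concern.** A non-converter needs the month-36 tests for the 3-year outcome to be established. A participant diagnosed earlier does not, because the outcome is already final. For that participant criterion (i) adds no outcome information. Nor does it measure adherence, which is the job of criterion (ii). It only makes inclusion depend on attendance after the event.

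If earlier converters miss the final OGTT at a different rate from non-converters, the set is selected on the outcome and the per-protocol risks are distorted. If that differs by arm, so is the comparison. In the time-to-event analyses the rule also conditions entry on the future: observed event intervals are discarded because of something that happens later, although these methods are built to use partial follow-up.

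**Working it through.** **Inputs from the article.** Sample size justification: 33% and 23% incidence by 3 years, 20% dropout, 423 per arm, 80% power, two-sided 5%. As a check on these inputs, the two-proportion formula with continuity correction gives 335 per arm. Then 335/0.8 = 419 per arm, 838 in total, within 1% of the stated 846.

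**Assumptions not in the article.** A constant hazard within each arm; 20% of non-converters and of month-36 converters lack month-36 tests (the planning dropout rate applied to them); a fraction q of earlier converters lacks the month-36 OGTT, with q varied. Losses under criterion (ii) are ignored.

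**Step 1: conversions found by month 30.** Early = 1 − (1 − risk)^(30/36).
- Control: 1 − 0.67^(30/36) = 0.2838, leaving 0.33 − 0.2838 = 0.0462 late (86% early).
- Intervention: 1 − 0.77^(30/36) = 0.1957, leaving 0.0343 late (85% early).

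**Step 2: risk in the per-protocol set.**

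Risk = [early × (1 − q) + late × 0.8] / [early × (1 − q) + late × 0.8 + (1 − risk) × 0.8]

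For example, control at q = 0.5: (0.1419 + 0.0370) / (0.1419 + 0.0370 + 0.5360) = 0.1789 / 0.7149 = 25.0%.

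| q, control | q, intervention | Control | Intervention | Difference (points) | Risk ratio |
|---|---|---|---|---|---|
| 10% | 10% | 35.3% | 24.8% | 10.5 | 0.70 |
| 20% | 20% | 33.0% | 23.0% | 10.0 | 0.70 |
| 50% | 50% | 25.0% | 16.9% | 8.1 | 0.68 |
| 80% | 80% | 14.9% | 9.8% | 5.1 | 0.66 |
| 50% | 20% | 25.0% | 23.0% | 2.0 | 0.92 |
| 20% | 50% | 33.0% | 16.9% | 16.1 | 0.51 |

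The rule is unbiased when q equals the loss in non-converters. It lowers both risks when q is higher and raises them when q is lower. With equal loss by arm the risk difference moves with the risks, while the risk ratio changes little.

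**Step 3: cost without bias.** Even at q = 20% in both arms, confirmed events are discarded: 423 × 0.2838 × 0.2 = 24 in control and 423 × 0.1957 × 0.2 = 17 in intervention.

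**Step 4: the obvious one-clause repair.** Suppose criterion (i) also admitted anyone diagnosed earlier, but still excluded untested non-converters. That is q = 0 in the formula:
- Control: 0.3208 / 0.8568 = 37.4%.
- Intervention: 0.2231 / 0.8391 = 26.6%.

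The difference is 10.8 points. Both risks are now inflated, because only non-converters can be lost before month 36.

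**The case against.** The strongest reply is that nothing in the article shows converters returning less often than others. Table 3 covers all participants and schedules FPG and OGTT at month 36. The secondary endpoints include change in FPG and 2-hour glucose to 3 years, with no exemption for converters. Under Retention of participants, the S$20 deposit comes back as S$80 to anyone who completes the last visit. If converters attend as scheduled, the rule does little harm.

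This stands. A reader might infer from the stopping of metformin at conversion that care changes, converters drop away, and the per-protocol result is therefore biased downward. The documents do not support that. The metformin sentence concerns only intervention participants on the drug and says nothing about visits or tests. The 50% and 80% rates are illustrations, and the direction is not fixed.

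The reply also notes that a requirement for end-of-study data is a familiar completer definition, that any per-protocol set selects on events after randomization, and that no conclusion is tied to this set in a superiority trial whose primary analysis is modified ITT. That limits the consequence and also stands. It does not supply a reason to discard an outcome already established.

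Finally, the handling of earlier-diagnosed participants could be left to a fuller document. But the article states the set in full, with two numbered criteria, and the objection is to what is stated. If study conclusion was meant as each participant's own endpoint, the text should say so. The natural reading is the month-36 visit, which Table 3 labels as the end of the study.

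**Conclusion.** The point holds in conditional form and is minor. As written, criterion (i) removes a confirmed converter who lacks the month-36 OGTT, from the binary and the time-to-event per-protocol analyses alike.

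Whether this biases anything depends on attendance that the documents do not give. There is none if converters and non-converters miss the final tests equally often. With greater loss in converters, equal by arm, the difference falls from 10 points to 8.1 (50% loss) or 5.1 (80% loss). With 50% loss in one arm and 20% in the other it is about 2 or about 16 points, depending on which arm loses more. These figures rest on the planning risks, a constant hazard and 20% loss in non-converters. Unequal return cannot be ruled out in an open-label trial whose intervention arm alone receives coordinator calls and weight-loss payments, but neither its presence nor its direction is shown.

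The primary modified ITT analysis and the multiple-imputation analysis of the ITT population are not touched.

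**What to change.** Drop criterion (i) and define the per-protocol set by criterion (ii) alone. The sessions it refers to fall in weeks 1 to 6, before the first follow-up glucose test at month 6, so membership would no longer depend on anything after the outcome. Then:

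- **Kaplan-Meier and interval-censored analyses:** run them on this set, with censoring at the last glucose test.
- **Binary 3-year risk:** count every diagnosis at an earlier study visit as an event, and handle non-converters without month-36 tests by the multiple imputation already planned for the ITT population.

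Do not merely add an exception for earlier diagnoses while still excluding untested non-converters; under the assumptions above that inflates both risks (37.4% vs 26.6%).

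The cost is a change to one definition and a little more analysis work. No additional data are needed.

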#### Secondary endpoints

Secondary endpoints include the change from baseline to end-of-study (3 years) in the following outcome measures:
HbA1cFPGTwo-hour plasma glucoseBody weightBMIWaist circumferenceDietary intake (assessed by the Food Frequency Questionnaire (FFQ) [32])MET-minutes per week (assessed by the International Physical Activity Questionnaire (IPAQ) [33])Health status scores (assessed by the EQ-5D-5L [34])Work productivity loss and activity impairment (assessed by the Work Productivity and Activity Impairment Questionnaire: General Health V2.0 (WPAI:GH) [35])

Secondary endpoints also include the proportion of participants who have engaged in the targeted level of physical activity (≥ 150 min/week of walking, moderate activity, or vigorous activity as defined by the IPAQ [33]).

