### Assessments and visit schedule

Baseline measurements (questionnaire completion, physiological and anthropometric measurement, retinal photography) are taken for all participants. Participants who are referred based on FPG alone also undergo a 75-g OGTT at the baseline visit. Follow-up visits are conducted at month 3 and every 6 months from the date of randomization (6, 12, 18, 24, 30, and 36 months). The acceptable tolerance in the 6-monthly visits is +/− 1.5 months. All assessments are performed by trained study coordinators following standard operational procedures and unaware of participants’ study group allocation. Study visits and assessments are summarized in Table 3. The assessments are described below.

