#### Sociodemographic information

Baseline sociodemographic information is collected to assess baseline imbalance, adjust for potential confounding in the statistical analyses, and stratify participants for subgroup analyses. The information collected include age, ethnicity, education, family history of diabetes, and health history.

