### Sample size justification

A study in the Chinese pre-diabetes population showed an 11% annual incidence of diabetes for participants who did not receive any intervention [39], which is equivalent to a 30% incidence of diabetes over 3 years. The study also showed that the relative risk (RR) for lifestyle interventions was 0.64. In addition, the Indian Diabetes Prevention Program study showed that the relative risk (RR) for lifestyle interventions and metformin was 0.72 and 0.74, respectively [5]. Risk ratios for Malays are assumed to fall between those of Indian and Chinese ethnicity. We assumed that the relative risk of converting to diabetes for those receiving intervention in multi-ethnic Singapore (composed primarily of Chinese, Malay, and Indian ethnicities) would be between the estimated effect sizes in the two cited studies; in particular, we used an RR of 0.70 for the intervention.

Given the above assumptions, we aim to recruit up to 846 participants across the two arms (423 participants per intervention arm and control arm). This will allow us to achieve 80% power with 5% two-sided type I error rate and 20% drop-out rate to detect a difference in intervention effect of 10% between the 2 study arms, assuming 33% and 23% incidence of diabetes by 3 years in the control and intervention arm respectively (RR = 0.70). The trial aims to show that the intervention is superior to the current standard of care.

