Secondary outcomes (engagement in ≥150 minutes of physical activity per week; change from baseline in the following outcomes: HbA1c, FPG, 2-hour plasma glucose, body weight, BMI, waist circumference, health status scores, MET-minutes per week and activity impairment score) will be analyzed using generalized linear models. Subgroup analyses will also be performed, with participants stratified by baseline age (< 50 years, ≥ 50 years), sex, pre-diabetes type (isolated IFG, isolated IGT, IFG + IGT), HbA1c (< 5.7%, 5.7–6.4%, ≥ 6.5%), family history of diabetes, BMI (23.0 to 27.4 kg/m^2^, ≥ 27.5 kg/m^2^), physical activity level (< 150 min/week, ≥ 150 min/week of physical activity), ethnicity (Chinese, Malay, Indian, others), and average monthly income (< S$5000, ≥ S$5000). Baseline characteristics, intervention adherence, and adverse events will be summarized using descriptive statistics.

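### The model named for the continuous secondary outcomes is a GLM of change at month 36; a baseline-adjusted repeated-measures model would also use the interim visits and hold up better against drop-out

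*Protocol article*

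**What the plan says.** Under Secondary endpoints, the article states: "Secondary endpoints include the change from baseline to end-of-study (3 years) in the following outcome measures". The list includes HbA1c, FPG, 2-hour glucose, weight, BMI, waist, MET-minutes and health status. Statistical analyses then says that the secondary outcomes "will be analyzed using generalized linear models". It names no covariates, analysis set or missing-data method for these models.

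The same section is fuller on the primary outcome. Its model is adjusted: "Potential confounders such as age, sex, family history of diabetes and FPG at baseline will be included as covariates". Multiple imputation appears as a sensitivity analysis in which "the imputed datasets will be analyzed using the same GLM and covariates as the primary effectiveness analysis".

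On timing, Assessments and visit schedule says: "Follow-up visits are conducted at month 3 and every 6 months from the date of randomization". Table 3 places the outcomes as follows:

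- Weight, waist and BMI (from weight and height): months 3, 6, 12, 18, 24, 30 and 36.
- HbA1c, FPG, EQ-5D-5L, IPAQ and WPAI:GH: months 6, 12, 18, 24, 30 and 36.
- 2-hour glucose: months 12, 24 and 36.

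Sample size justification allows for a "20% drop-out rate".

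**The concern.** A GLM of change at month 36 takes one follow-up value per person. Unless missing values are imputed, someone last seen at month 24 adds nothing to it, even with four or five recorded weights.

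Precision is the smaller matter. The larger one is that drop-out may be related to outcome, and differently in the two arms. Under Financial incentives, intervention participants are paid at a visit only if they hold the 5% weight loss; controls have no such payment. An intervention participant who regains weight therefore loses a reason to attend that a control never had. If that drives drop-out, a month-36 comparison among those who remain flatters the intervention. The retention measures (reminders, deposit, 6-monthly draws) apply to both arms and do not remove the asymmetry.

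**Working it through.** **Planned numbers.** The article gives no sample-size figure for the secondary outcomes, so the primary one is reproduced first. Two proportions of 33% and 23%, two-sided 5%, 80% power, with continuity correction, need 335 per arm. Then 335/0.80 = 419 per arm, or 838 in total, which is 1.0% below the stated 846. The 20% allowance can therefore be taken at face value: 0.20 × 846 = 169 participants without a month-36 value, and 0.80 × 423 = 338 per arm with one.

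**Baseline adjustment.** Let r be the correlation between the baseline and month-36 values. The article does not give it; 0.5 to 0.9 is assumed. In units of the outcome variance, and assuming equal variances at the two times:

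- unadjusted change score: 2(1 − r)
- change adjusted for baseline: 1 − r²
- ratio: (1 − r²) / [2(1 − r)] = (1 + r)/2

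The detectable difference at 80% power with 338 per arm is (1.960 + 0.842) × √(variance × 2/338).

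| r | Variance saved | Detectable difference, unadjusted (SD) | Detectable difference, adjusted (SD) |
|---|---|---|---|
| 0.5 | 25% | 0.216 | 0.187 |
| 0.7 | 15% | 0.167 | 0.154 |
| 0.9 | 5% | 0.096 | 0.094 |

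This saving exists only if the GLM omits the baseline value. If baseline is included, the saving is already in hand.

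**Repeated visits.** The comparison here is between a repeated-measures model and a baseline-adjusted month-36 model in those who remain. It assumes six post-baseline visits and 20% drop-out accruing evenly. The information at each drop-out pattern is the inverse of the covariance of the visits observed, conditional on baseline; these are summed in proportion to the patterns, and the month-36 element of the inverse is read off. The further variance reduction is:

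- compound symmetry, r from 0.5 to 0.9: 3% to 6%
- AR(1), adjacent-visit correlation 0.80 to 0.95: 5% to 8%

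With the three visits at which 2-hour glucose is measured, the same calculation gives about 2% to 6%.

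The two gains multiply. Under compound symmetry at r = 0.5, 0.75 × 0.967 = 0.725, a total saving of about 27%. At r = 0.9, 0.95 × 0.943 = 0.896, about 10%.

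**Possible bias.** This is an illustration with assumed inputs. Drop-out is 20% in both arms. It is random in control; in the intervention arm its odds rise 1.5-fold or 2-fold per SD of worse earlier change. The correlation between earlier and month-36 change is ρ. The bias among those who remain is ρ times the mean shift in earlier change among those retained.

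| Odds ratio per SD | ρ = 0.5 | ρ = 0.85 |
|---|---|---|
| 1.5 | 0.04 SD | 0.07 SD |
| 2.0 | 0.06 SD | 0.11 SD |

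The standard error of the arm difference is √(2/338) = 0.077 SD, so the bias runs from about 0.5 to 1.4 standard errors, in favour of the intervention. A model that includes the earlier values removes it when drop-out depends only on those recorded values.

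**The case against.** A reader might infer that the secondary models have no baseline adjustment and that everyone lost before month 36 is dropped. The article supports neither reading. A GLM of change can carry the baseline value as a covariate. Under Sociodemographic information the article says baseline data are collected partly to "adjust for potential confounding in the statistical analyses", although the items listed there are demographic and history variables, not each outcome's own baseline. No analysis set or missing-data rule is stated for the secondary outcomes, and nothing says imputation is withheld from them. A condensed article may leave both to the full protocol or SAP, so the silence is not itself a fault.

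It is also tempting to argue that selecting people on high glucose biases a change score through regression to the mean. Both arms meet the same entry criteria and are randomized 1:1, so the expected regression is equal and cancels in the contrast. Only precision and chance imbalance are at issue.

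Nor can it be said that every secondary confidence interval is too wide: if baseline is already in the model, what is left to gain is a few per cent of variance.

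Finally, month-36 change is a legitimate endpoint, and a baseline-adjusted month-36 model with good imputation is a valid analysis. A normal-theory mixed model may suit MET-minutes or a 0 to 10 impairment rating poorly. All of this stands, and it limits the point. It does not alter the fact that the one model named is for a single time point while the interim data are scheduled.

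**Conclusion.** The point holds as a better method than the one named; it is not an error or contradiction in the article. The gain in variance is about 3% to 8% from the repeated visits if baseline is already in the GLM, with a further 5% to 25% (r from 0.9 to 0.5) if it is not. All correlations are assumed.

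The stronger reason is validity. A month-36 GLM without imputation can be biased when drop-out depends on earlier weight or glucose, which is plausible because weight-contingent payments exist in one arm only. The sizes shown rest on an assumed drop-out mechanism, and the 20% is a planning allowance, not an observed rate. A repeated-measures model protects against dependence on recorded values, not on unrecorded ones. Only secondary outcomes are affected.

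**What to change.** For each continuous secondary outcome, specify a repeated-measures model over all scheduled post-baseline visits (months 12, 24 and 36 for 2-hour glucose). Include arm, visit, arm-by-visit, that outcome's own baseline value with its visit interaction, and the primary-model covariates. Report the month-36 arm contrast, so the endpoint itself does not change.

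For clearly non-normal outcomes such as MET-minutes and activity impairment, use a suitable link, a transformation, or a baseline-adjusted month-36 GLM with multiple imputation from the earlier visits.

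If the full protocol or SAP already covers baseline adjustment and missing month-36 values, confirm this and add only the use of the interim visits. The cost is a change of wording and slightly more analysis work. No visit or measurement is added.
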